**Intended/Potential Use of the Study Findings**

A recent study comparing the cost-effectiveness of HIV prevention interventions found that the two most important factors that determined cost-effectiveness were the HIV prevalence of the target population and the cost per person reached.30 In fact, one of the two most cost-effective interventions overall was showing videos in STI clinics (individual-level).30 These findings support our proposed online behavioral intervention using video vignettes in terms of cost-effectiveness and reaching high-risk MSM. If successful, this type of novel Internet-based intervention approach will be efficient, cost-effective, feasible to replicate, and especially useful in reaching men in rural areas or other hard-to-reach populations.

Specific Aims and Hypotheses

**Aim 1:** To test the feasibility of implementing an innovative national online randomized controlled, multi-branched, behavioral intervention for men who have reportedoral or anal sex with any male (new partner or not) in the past 60 days AND reported oral, anal or vaginal sex for the first time (new partner) with a male or female within the past 60 days.

**Aim 2:** a) To identify and recruit men who have sex with men met online or offline, and who, in the last 60 days, met a new sex partner; b) To enroll and randomly assign 3,000 MSM, representing diverse race/ethnicities and geography, into one control or four intervention conditions; c) To maximize retention 60-days post-intervention to complete the follow-up survey.

**Aim 3:** To evaluate the intervention conditions by comparing outcome risk measures (HIV disclosure, HIV testing, condom use, drug and/or alcohol use before sex, and depressive and/or anxiety symptomatology) at 2 time points for 5 study conditions.

**Aim 3 Primary Hypotheses:** Between baseline and 60-day follow-up there will be an increase in the following: a) HIV disclosure with new sex partners, b) HIV testing, and c) condom use in intervention branches 3, 4, and 5, compared to branches 1 and 2.

**Aim 3 Secondary Hypotheses:** Between baseline and follow-up, there will be a decrease in the following: a) drug use before sex, b) alcohol use before sex, and c) depressive and/or anxiety symptomatology in intervention branches 3, 4, and 5, compared to branches 1 and 2.

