**Evaluation of Branches**

Participants in all branches will be scheduled to complete three quantitative surveys including a baseline assessment, a brief immediate post-intervention assessment (or immediate post-baseline assessment for the control group) measuring intent to change behavior during the next 60 days, and a 60-day follow-up assessment. Additionally, we will record the number of “clicks” on the resources webpage (presented after the post-intervention assessment) which represent intent to access health services and information. Our 5-branch design will allow us to directly compare, within and across branch, changes in primary and secondary outcome behaviors from baseline to 60 days follow-up. By doing so, we will be able to measure the efficacy of each of the study branches, as compared to the control branch and standard text-based prevention branch and relative to each other. The multi-branch design will allow us to directly compare the video-based interventions to the text-based prevention web-page to determine which branch elicits the most significant change in behavior.

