**Sampling, Sample Size, and Statistical Power**

The three primary outcomes in this study are increased HIV testing, HIV disclosure, and condom use. Using historical data from the pilot intervention (see Appendix A), we observed that HIV testing increased from 20% to 42% in HIV-negative men between baseline and 3-month follow-up. Based upon these values using a 2-group design (control vs. intervention), with a 5% significance level and 80% power, 77 participants would be required in each study condition for a total sample size of 154. In the current study, which has a 5 branch design, we anticipate that by enrolling 3,000 men and retaining 70% (N=2,111), we will have sufficient power to detect meaningful differences in behavior among the study branches.

Although we will be comparing within and across all study branches, we expect the greatest differences to be found between control branch 1 and branch 5 (both videos) for the primary outcomes. The Bonferroni correction will be used to protect the overall Type I error rate with multiple comparisons. In these comparisons, the nominal significance level will be set to alpha = 0.05 for two-sided tests (divided by the number of pairwise comparisons for individual tests). Using Chi-square tests to detect behavioral changes between the binomial primary outcomes, we obtain the following powers to detect a difference between two study branches for various true proportions and sample sizes (α=0.05; 10 pairwise comparisons).

| **Power Calculations for Meaningful Differences**  **between Study Branches** | | | | | |
| --- | --- | --- | --- | --- | --- |
| **Behavior Change Outcomes†** | | **Sample Size per Branch* and Associated Power** | | | |
| Branch A | Branch B | N = 300 | N = 400 | N = 500 | N = 600 |
| 0.10 | 0.15 | 0.142 | 0.221 | 0.308 | 0.396 |
| 0.10 | 0.20 | 0.709 | 0.865 | 0.944 | 0.979 |
| 0.10 | 0.25 | 0.978 | 0.997 | >.999 | >.999 |
| 0.15 | 0.20 | 0.097 | 0.150 | 0.210 | 0.275 |
| 0.15 | 0.25 | 0.569 | 0.747 | 0.863 | 0.931 |
| 0.15 | 0.30 | 0.939 | 0.988 | 0.998 | >.999 |
| 0.20 | 0.30 | 0.476 | 0.652 | 0.784 | 0.874 |
| 0.20 | 0.35 | 0.894 | 0.971 | 0.993 | 0.999 |
| 0.20 | 0.40 | 0.994 | >.999 | >.999 | >.999 |
| 0.30 | 0.40 | 0.375 | 0.536 | 0.673 | 0.780 |
| 0.30 | 0.45 | 0.821 | 0.936 | 0.980 | 0.994 |
| 0.30 | 0.50 | 0.984 | 0.998 | >.999 | >.999 |
| 0.40 | 0.50 | 0.336 | 0.488 | 0.623 | 0.733 |

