**Multivariate Analysis:** For dichotomous outcomes, we will use logistic regression models to simultaneously examine the effects of predictors found to have a statistically significant association with the binary outcomes in bivariate analyses. Further, logistic regression will allow the introduction of the pretest observation (e.g. asked new partner’s HIV status) and treatment status as predictors and a set of demographic control variables. For continuous outcomes, we will use linear regression models to study quantitative outcome variables such as number of days respondent drank alcohol in the past 60 days (at baseline and 60-day follow-up).

**Analysis of Treatment Branches:** For analysis of within-treatment branches, we will use McNemar’s Test, which is a chi-square test used when data consist of paired observations on a particular outcome (i.e., pre-post treatment design), such as HIV disclosure with a new sex partner. For analysis of between-treatment branches, we will test differences across interventions or group mean differences by employing linear regression with interaction terms. We will also use ANOVA to examine within- and across-branch differences between those who complete the intervention activities and those who do not.

**Safeguarding against Confounding:** To safeguard against confounding in the multivariate logistic regression models, variables not significantly associated with outcomes in simple bivariate analyses may be included for conventional demographic items or if it is highly plausible (either biologically or behaviorally) that they are associated with the outcome.

**Interactions:** Tests for interactions will be conducted between pairs of explanatory factors and binary outcomes to assess possible interactions.

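### The power table is for a one-time-point chi-square at alpha 0.005, but the between-branch comparison is assigned to linear regression with unnamed interaction terms, and interactions are tested at 0.10

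*Protocol*

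**What the plan says.** **Power.** Under Sampling, Sample Size, and Statistical Power the protocol writes "Using Chi-square tests to detect behavioral changes between the binomial primary outcomes, we obtain the following powers to detect a difference between two study branches". The table runs "for various true proportions and sample sizes (α=0.05; 10 pairwise comparisons"), with the 5% level split over the pairs. This gives 0.005 per test.

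**Effect of interest.** The Aim 3 primary hypotheses open with "Between baseline and 60-day follow-up there will be an increase in the following" and set branches 3, 4 and 5 against branches 1 and 2. Evaluation of Branches says that the design allows the team to "directly compare, within and across branch, changes in primary and secondary outcome behaviors from baseline to 60 days follow-up".

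**Analysis.** In Data Handling and Analysis, the paragraph Analysis of Treatment Branches gives the within-branch comparison to McNemar's test. For the comparison between branches it says "we will test differences across interventions or group mean differences by employing linear regression with interaction terms". It does not say which variables interact.

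**Alternative model.** Two paragraphs in the same section matter here. Multivariate Analysis describes, for dichotomous outcomes, a model in which "logistic regression will allow the introduction of the pretest observation (e.g. asked new partner’s HIV status) and treatment status as predictors". The opening paragraphs set every interaction test at 0.10.

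**The concern.** The method assigned to the between-branch comparison is not the method behind the table, and the protocol gives two significance levels that could apply to it.

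The effect is described as a change compared across branches, and the between-branch sentence follows directly on a pre-post test. A branch-by-time interaction is therefore the natural reading. Such a test carries the sampling noise of both surveys, so with weak correlation it needs more men than a follow-up comparison does. The table, which supports the claim of sufficient power with 3,000 enrolled, would then not describe the test being run.

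If the 0.10 rule applies instead, power is adequate, but ten pairwise comparisons at 0.10 abandon the control of overall type I error that the sample size section promises. Either way, a reader cannot tell which model and alpha decide the primary hypothesis.

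**Working it through.** **Inputs from the protocol.** Printed row 0.20 v 0.30: 0.476, 0.652, 0.784 and 0.874 at N = 300, 400, 500 and 600 per branch. Alpha is 0.05/10 = 0.005 two-sided, so z = 2.807. Expected completers are 600 − 240 = 360 in branches 1 and 2, and 600 − 180 = 420 in branches 3 to 5. **Assumed:** the baseline to follow-up correlation rho, which the protocol does not give.

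**1. Reproduce the table.** Two independent proportions with continuity correction:

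power = Φ{ [ |p1 − p0| − 1/n − z·√(2p̄(1−p̄)/n) ] / √[(p0(1−p0) + p1(1−p1))/n] }

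For 0.20 v 0.30 this gives 0.471, 0.648, 0.781 and 0.872. All 52 cells are reproduced, with a largest deviation of 1.3 points. Without the correction, N = 400 gives 0.678. No baseline value and no correlation enter.

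**2. Difference in change at alpha 0.005.** Both branches start at p0, the Branch A rate. Branch A stays there and Branch B moves to p1. Per branch, with f the follow-up rate:

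Var(change) = p0(1−p0) + f(1−f) − 2·rho·√[p0(1−p0)·f(1−f)]

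For 0.20 v 0.30, N = 400, rho = 0:
- Branch A: 0.16 + 0.16 = 0.32. Branch B: 0.16 + 0.21 = 0.37.
- SE = √[(0.32 + 0.37)/400] = 0.0415.
- Power = Φ(0.10/0.0415 − 2.807) = Φ(−0.399) = 0.345.

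| 0.20 v 0.30, alpha 0.005 | printed | rho 0 | 0.3 | 0.4 | 0.5 |
|---|---|---|---|---|---|
| N = 400 | 0.652 | 0.345 | 0.527 | 0.616 | 0.722 |
| N = 600 | 0.874 | 0.556 | 0.762 | 0.840 | 0.912 |
| 360 v 420 | not tabulated; one-time-point test without correction 0.655 | 0.334 | 0.512 | 0.601 | 0.708 |

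For 0.20 v 0.40 at N = 400 and rho = 0, power is still 0.97.

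**3. Break-even correlation.** Setting the variance in step 2 equal to that of the follow-up comparison gives rho = A/(A + √(AB)), with A = p0(1−p0) and B = p1(1−p1). This is 0.43 for 0.10 v 0.20, 0.47 for 0.20 v 0.30 and 0.49 for 0.40 v 0.50.

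**4. Same test at the 0.10 interaction level.** z = 1.645. For 0.20 v 0.30 at N = 400, power is Φ(2.408 − 1.645) = 0.777 at rho 0 and 0.891 at rho 0.3, both above 0.652. At N = 600 and rho 0 it is 0.904, against 0.874.

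**5. Baseline-adjusted follow-up model at 0.005.** In a linear approximation the follow-up variance is multiplied by (1 − rho²). For N = 400, SE = √[(0.16 + 0.21)(1 − rho²)/400], and power is 0.685, 0.739 and 0.839 at rho 0, 0.3 and 0.5.

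**6. What the protocol hints about rho.** Appendix A reports testing rising from 20% to 42% with OR 2.8. If that is a matched-pair OR:
- the smaller discordant share is 0.22/1.8 = 0.122 and the larger is 0.342;
- the share tested in both periods is 0.42 − 0.342 = 0.078;
- rho = (0.078 − 0.084)/√(0.16 × 0.2436) ≈ −0.03.

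The unpaired OR is (0.42/0.58)/(0.20/0.80) = 2.90, so 2.8 does not settle which kind was reported. This is suggestive only, and only for HIV testing.

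**The case against.** A reader might infer that the branch comparison, run as written, simply lacks the tabulated power and will probably miss a real 10-point effect. The protocol does not support that, for these reasons.

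- **The interaction is not named.** Branch by time is an inference. The Interactions paragraph speaks of pairs of explanatory factors, so branch by covariate is also possible.
- **The 0.10 rule.** An interaction test under the protocol's own level has more power than the table, even at rho 0. This stands as arithmetic. It does not rescue the plan, because it gives up the 0.005 per test on which the table was calculated.
- **Logistic regression is already there for dichotomous outcomes.** With treatment status and the pretest value as predictors, it is a between-branch comparison. This largely stands, and it makes the fix easy. But it sits in a general paragraph that selects predictors by bivariate significance, and the next paragraph gives the branch comparison to another method. Linear regression may have been meant for the disclosure scales, which the outcome table treats as continuous. The text does not say so, and the power section calls the primary outcomes binomial.
- **The table is labelled as behavior change.** If its proportions are shares of men who changed, a chi-square already tests change. The footnote, however, equates them with the primary outcomes themselves.
- **Rho is assumed.** This stands. At rho 0.4 and N = 400 the shortfall is under 4 points, and at 0.5 the difference-in-change test beats the table.

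**Conclusion.** The mismatch is established from the protocol alone. The table is for a chi-square at one time point at 0.005. The between-branch method is a linear regression with unspecified interactions, under a section rule of 0.10.

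The power consequence is conditional. It needs three things together: a branch-by-time interaction, retention of the Bonferroni alpha, and a low correlation. Under those, a 10-point difference may be missed more often than the table implies: 0.345 to 0.62 for rho 0 to 0.4, against 0.652, for 0.20 v 0.30 at 400 per branch. Outside those conditions the loss is small, absent or reversed. If the 0.10 level is used, the cost falls on type I error instead of power.

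This is more than detail left to a later analysis plan, because the stated method and alpha differ from those on which the sample size rests.

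**What to change.** In Data Handling and Analysis:

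- Make the between-branch test of the binary primary outcomes a logistic regression of the 60-day outcome on branch, adjusted for the same outcome at baseline. Always include branch and the baseline value; do not select them by bivariate significance.
- State that these branch comparisons use the Bonferroni alpha from the sample size section.
- Limit the 0.10 interaction level to exploratory effect modification.

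The existing power table can then stand as a slightly conservative guide.

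If a branch-by-time test is kept, name it, account for the pairing of the two surveys within each man, and restate power at the Bonferroni alpha over a stated range of correlation.

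The cost is wording only. The baseline value is already collected and the model is already described, so no data or participants are added. The one downside is that results are reported as baseline-adjusted follow-up differences instead of raw change.

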**Data Collection Procedures**

As participants complete each section of the online survey, the data will immediately be transferred to a Public Health Solutions designated server that cannot be accessed publicly. At the completion of data collection, an analytic file will be prepared by the Manager of Web Development and given to the data analyst in the Research and Evaluation Unit. The survey file, which has no personal identifiers, will be removed from the server and stored in a secure site. Only the study investigators and CDC collaborators will have access to the data. Because the analytic file has no personal identifiers, a CD will be kept in a locked file in the PI’s office for up to 10 years.

**Protection of Privacy/Confidentiality**

Participants will be assigned a unique study number. Behavioral survey (baseline, immediate post-intervention, 60-day follow-up) data will only include this unique study number. Email addresses of participants who agree to provide this information will be stored in an electronic file separate from survey data on a secure, firewall protected Public Health Solutions-managed server. The electronic file will contain email addresses linked to a participant’s unique study number. This linking file is necessary to identify and contact participants for the 60-day follow-up survey and track the result (i.e., completed follow-up or not). This file will be destroyed after the data collection period (i.e., 60-day follow-up assessments have been completed). Only the Public Health Solutions Manager of Web Development and Programming will have access to these files. Even in the highly unlikely event of a breach of the security system, the survey data exist only as a string of numbers with a few qualitative responses. The analytic data file has no personal identifiers and access will be limited to study staff.

**Lack of Need for Assurance or Certificate of Confidentiality**

We do not anticipate that any formal confidentiality protections will be needed for this research. While the behavioral assessments will include responding to some sensitive questions related to sexual behavior, sexual orientation, and drug use, participants’ names will not be collected. In conducting previous research with similar target populations, we have not observed that individuals have expressed reluctance to participate unless we are able to promise confidentiality. We also have no reason to doubt the validity of responses without the expectation of complete confidentiality.

**Information Management and Analysis Software**

The Web Development and Programming staff will program the surveys and electronic consent forms, and program computerized randomization for consenting intervention participants. Completed baseline and follow-up surveys will be downloaded into a SQL database, and then cleaned for missing data and incomplete cases. Statistical Software for the Social Sciences (SPSS) Version 14.0 and SAS 9.1 will be used for data cleaning and analysis.

**Data Management**

Public Health Solutions will utilize a web-based data monitoring tool to track recruitment and survey completion. There will be no way to identify participants using this tracking tool. Public Health Solutions will regularly report tracking tallies (with no person-level identifiable data) as the data collection period progresses. The assessment data will be encrypted and transferred routinely to CDC using a secure data network system. As in all of our other online studies, after data collection, we will thoroughly clean and conduct contingency checks on the data to ensure high quality of data, in terms of completeness and accuracy. We will report on the overall completion rate for the intervention, as well as the different steps in the consent process. The data will be released in SPSS and SAS formats to other investigators, although the data can be converted to other statistical software packages, such as STATA. We may require a data-use agreement with interested parties, depending on the variables being requested and whether the requested data have already been published or not. After cleaning and analyzing the data, we will report the strengths and limitations of the dataset, in terms of recommendations for data analysis, reporting, and interpretation.

**Quality Assurance**

After data collection, data will be checked for reliability and validity of value entries, and consistency across data elements. Since the provision of an email address is a requirement for participation in the intervention study, it is unlikely that duplicate records will be an issue for this study. However, the study team will be unable to identify if an individual has enrolled into the study more than once using differing email addresses. Should this occur the duplicative data will likely remain in the data file. This occurrence is likely to be infrequent, considering the lack of a large incentive. All quality assurance measures taken during data collection will be documented and made available to collaborators. Finally, to guard against bias in the analysis and interpretation of the data, analyses will be performed and reviewed by both scientists at Public Health Solutions and CDC.

**Bias in Data Collection, Measurement, and Analysis**

In order to eliminate or reduce possible bias in the proposed intervention, we will be programming the baseline survey to select and randomly assign participants who consent to be part of the study. There will be no human involvement in the process of selecting and assigning participants. Participants will not be blinded once they are randomized to their treatment or control condition, however they will be told very little about the other possible conditions (See Appendix C for the consents). This will minimize multiple attempts to enroll in the study in order to achieve a different assignment. It is still possible that a participant could attempt to complete the baseline survey several times; however, given the length of the survey and absence of incentives this is unlikely.

**Intermediate Reviews and Analysis**

During the data collection phase, we will conduct random checks of the data to ensure proper collection into the SQL database.

**Response to New and Unexpected Findings/Changes in Environment**

If during data collection there is a significant external event (e.g., the announcement of a fast-spreading, multi-drug-resistant HIV strain), we can immediately respond by altering the survey online to ask additional questions in response to this event.

**Limitations of Study**

There are several limitations to consider in this study.

1. Minority MSM may be under-represented in this sample; however the study team will monitor this during the course of enrollment. It may be necessary to increase the projected enrollment figures in order to achieve an adequate sample of this population. Any adjustments in enrollment figures will be submitted as an amendment to local and CDC IRBs.
2. Similar to mail-in, phone, and other non-face-to-face survey research, the study team will be largely unable to verify the identity of participants or the reliability of responses to the survey instruments.
3. It is not possible for the study team to determine whether this study population is representative of MSM using the internet, or MSM in general given that this population has never been enumerated.

